**Sampling: Consecutive sampling.**

Estimated study date: June, 2020

Estimated primary completion date, August 2020

Estimated study completion date: September, 2020

**Inclusion Criteria:**

- At least 18 years of age
- COVID-19 infection, confirmed by polymerase chain reaction (PCR) test
- Mild to moderate COVID-19 infection

**Exclusion Criteria:**

- Not willing to participate.
- Discontinue duties for any reason during the specified period
- Presence of haemoglobinopathies or other blood disorders.

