**Summary**:

Since December 2019 COVID-19 is dominating the life of the people of this universe. Its behavior also varied among the nations of the universe. The risk factor of adverse outcome of COVID-19 was determined. No biologic markers for the susceptibility of the infection is yet to be found. The relation of blood group and infection was found in several disease like cholera, severe malaria, severity of dengue, H-pylori infection have been elucidated. Genome wide Association Study of Severe Covid-19 with Respiratory Failure, GWAS Group detected cross-replicating associations with rs11385942 at locus 3p21.31 and with rs657152 at locus 9q34.2. The association signal at locus 9q34.2 coincided with the ABO blood group locus. Several studies also found some contradicting results in this regard.

So to observe the impact of ABO blood groups on the presentation and outcome of Confirmed COVID -19 infection, this study was conducted in the largest COVID19 dedicated hospital in Bangladesh. It would be a prospective cohort study. A cohort of the patients with RT-PCR positive COVID-19 patients since June 2020 till September 2020 will be included in this cohort. Their blood group will be determined. The clinical features, severity, time required to recover, conversion of severity, Persistence of RT-PCR positivity 14 days after initial positivity will be determined. They will be followed up for at least 30 days or hospital discharge which one is longer. Comparison will be made in different blood groups.

The primary outcome would be the duration required to have clinical improvement.

Data will be analyzed using SPSS 20. To compare the groups one way ANOVA was done for continuous variable, Chi square for categorical variables. For outcome assessment relative risk (RR) with 95% CI was measured for qualitative variable categorizing blood group A and non A. survival analysis by Kaplan-Meier curve was done for the duration of recovery. Result of the study and statistical analysis will be presented by tables, figures, graphs, diagrams, charts and photographs. All these will have own legends (i.e. title) and will be serially numbered. Discussion will be done on the basis of result obtained from the study and comparing with similar studies done at home and abroad. Summarization will be drawn after discussion. Conclusion will be drawn depending upon the results and discussion.

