**3. RATIONALE:**

Covid-19 is an emergent pandemic, threatens the life of millions of the people throughout the globe. The severity, outcome and susceptibility varies among the nations, race and individuals. Biologic markers of COVID-19 infection is still uncertain. Several studies revealed blood group A is most susceptible. The studies were performed with the affected patients only. This study Aim to observe the impact of different blood groups on presentation and outcome of confirmed COVID-19 infection. It would help us to detect a biologic marker for the susceptibility and outcome of COVID-19 infection.

1. **METHODOLOGY:**

Study type: Prospective cohort

Sample size:

Proportions to cure from COVID-19 by day-12 in group-1(blood group A) and group-2 (blood group Assuming expected B, O, AB) are 0.70 and 0.90 respectively. Thus we need a total of 378 samples at 1:2 ratio, and, that would provide a power of at least 90% at two tailed test where p value less than 0.05 to detect significant difference between the groups. Considering 10% dropout, we need 416 samples in total.

$$n=\frac{r+1}{r}\frac{p^{*}\left( 1-p^{*} \right){(Z_{\beta}+Z_{\frac{\alpha}{2}})}^{2}}{{{(p}_{1}- p_{2})}^{2}}$$

r = ratio of group-1 and group - 2

p*= Average of proportion

Z_α/2_ = Level of significance

Z_β_ = Power of the test

p_1_ - p_2_= Effect size

p_1_ = Proportion in group - 1

p_2_ = Proportion in group - 2

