**Primary Outcome Measure:**

- 1. Duration required to have clinical improvement

[Time Frame: 1 months]

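### The exclusion for discontinuing duties is undefined and can be judged only after enrolment, so it can bias the A versus non-A comparisons by an amount the protocol does not determine

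*Protocol*

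**What the plan says.** The Exclusion Criteria in the main protocol list "Discontinue duties for any reason during the specified period", and the abstract for the National Research Ethics Committee repeats the line word for word. No section defines the duties or the period.

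The rule sits in a design described as "Study type: Prospective cohort" with "Consecutive sampling". On follow-up, the Summary states: "They will be followed up for at least 30 days or hospital discharge which one is longer". The primary outcome is "Duration required to have clinical improvement", with a one-month time frame. The Data analysis section plans a relative risk with 95% CI for blood group A against non-A, and a Kaplan-Meier analysis of the duration of recovery.

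The sample-size text assumes day-12 cure proportions that "are 0.70 and 0.90 respectively" for A and non-A. It also provides for loss: "Considering 10% dropout, we need 416 samples in total".

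**The concern.** An eligibility criterion should rest on facts known when the patient enters. This one depends on something that happens, or does not happen, during follow-up. Applied as written, it decides who belongs to the cohort after part of the outcome has been seen.

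The wording allows two readings, and neither can be applied at enrolment:

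- **Study participation.** Stopping for any reason could cover withdrawal, transfer, worsening, death, or leaving early because of recovery. Several of these are close to the outcomes being measured.
- **Work duties.** The subjects are hospital patients with confirmed COVID-19. Those with a job would generally not be working while admitted, so the rule could remove most of them.

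At stake is the main comparison. If the patients removed differ in outcome from those kept, or if removal works differently in group A and non-A, then the relative risk and the recovery curves describe a selected remainder and not the enrolled cohort.

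**Working it through.** **The plan's own allowance.** 378 × 1.10 = 415.8, rounded up to 416. The plan therefore expects about 416 − 378 = 38 patients to be lost. The figure of 378 is taken here as stated, because nothing below depends on how it was obtained.

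**Inputs.** From the sample-size text: cure by day 12 of 0.70 (A) and 0.90 (non-A), a 1:2 ratio, and 10% loss. These are the only group-specific rates in the protocol, so they stand in for the outcome. All removal rates below are assumptions, chosen so that 10% is removed overall. For the cases with no true difference, both groups have the pooled rate (0.70 + 2 × 0.90)/3 = 0.833.

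**Formula.** Let p be the true cure proportion, c the fraction of cured patients removed and u the fraction of uncured patients removed. Then

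observed cure = p(1 − c) / [p(1 − c) + (1 − p)(1 − u)].

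**Cases.**

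1. Removal unrelated to outcome (c = u = 0.10 in both groups).
2. Only uncured patients removed, with the same fraction u = 0.60 in both groups. A: 0.70/(0.70 + 0.30 × 0.40) = 0.70/0.82 = 0.854. Non-A: 0.90/(0.90 + 0.10 × 0.40) = 0.90/0.94 = 0.957. Removed overall: (0.18 + 2 × 0.06)/3 = 0.10.
3. Only uncured patients removed, 15% of A and 7.5% of non-A. A: 0.70/0.85 = 0.824. Non-A: 0.90/0.925 = 0.973. Removed overall: (0.15 + 2 × 0.075)/3 = 0.10. This means removing 0.15/0.30 = 50% of A's uncured patients and 0.075/0.10 = 75% of non-A's.
4. No true difference; c = 0.05 and u = 0.35 in both groups.
5. No true difference; c = 0.05 and u = 0.35 in A, c = u = 0.10 in non-A.

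| Case | Cure, A | Cure, non-A | Difference (non-A − A) | RR for cure | RR for non-cure |
|---|---|---|---|---|---|
| Truth behind cases 1–3 | 0.700 | 0.900 | 0.200 | 0.778 | 3.0 |
| 1 | 0.700 | 0.900 | 0.200 | 0.778 | 3.0 |
| 2 | 0.854 | 0.957 | 0.104 | 0.892 | 3.4 |
| 3 | 0.824 | 0.973 | 0.149 | 0.846 | 6.5 |
| Truth behind cases 4–5 | 0.833 | 0.833 | 0 | 1.00 | 1.00 |
| 4 | 0.880 | 0.880 | 0 | 1.00 | 1.00 |
| 5 | 0.880 | 0.833 | −0.046 | 1.06 | 0.72 |

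Cases 1 and 4 show no bias in the comparison; cases 2, 3 and 5 do. In case 3 the difference shrinks and the RR for cure moves towards 1 (0.824/0.973 = 0.846), while the RR for non-cure more than doubles, to (0.15/0.85)/(0.025/0.925) = 0.176/0.027 = 6.5. The Data analysis section does not say which event its relative risk counts, so even the direction of the distortion is open.

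**The case against.** **The line may be a stray.** The protocol gives patients no duties, and the case record form has no field for occupation or for discontinuation. The section on utilization of results describes a doxycycline and ivermectin study, and the summary for the ethical committee calls this study experimental. Text carried over from another protocol is therefore plausible, though not proven. If so, the rule might never be applied. It nevertheless stands in both exclusion lists, and removing it costs almost nothing.

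**The study means to keep patients who worsen.** Conversion to the next level of severity is a secondary outcome, and follow-up runs for at least 30 days. The criterion does not name death, transfer or deterioration. This stands: one cannot say who would in fact be removed. But the wording admits any reason, so those patients are not protected either.

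**Stronger readings that a reader might infer, and that the protocol does not support:**

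- *That every blood-group comparison is biased.* Cases 1 and 4 show otherwise. Bias requires stopping to be related to outcome or to differ by blood group.
- *That the association is necessarily weakened.* Case 3 weakens it on one scale and strengthens it on another, and case 5 creates one where none exists. The removal rates are not in the protocol. Patients not cured by day 12 may also still improve within the month.
- *That the rule contradicts the 10% dropout allowance.* Enrolling 416 to retain 378 is compatible with leaving out those who stop.
- *That it contradicts the Kaplan-Meier plan.* The method could keep such patients to last contact, but the protocol names it without stating an analysis set or censoring rule. Those details may sit in an analysis plan that is not at hand, and their absence is not the fault raised here.

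**Conclusion.** The concern holds in a limited form. The criterion uses undefined terms and cannot be assessed at enrolment on either reading. Applied as written, it selects a consecutive prospective cohort by follow-up events. This is a defect in a rule the protocol states, not a detail left for later.

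The consequence is a risk of bias, conditional on stopping being related to outcome or differing by blood group. The protocol gives no ground for assuming that neither is so. About 38 patients, the plan's own dropout allowance, indicates the scale if the rule is read as study participation. Under the work-duties reading it could be far larger, but occupation is not recorded and no figure can be given. The table shows what assumed removal rates would do. It does not estimate the bias in this study.

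**What to change.** Delete the criterion from the Exclusion Criteria in the main protocol and in the National Research Ethics Committee abstract, so that exclusions rest only on facts known at enrolment. Then state the following:

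- Every eligible, consented patient stays in the analysis set.
- For time to clinical improvement, withdrawals and losses are censored at last contact. Deaths are counted as not improved through the one-month time frame; that is, they stay at risk without the event and are not censored at death.
- Numbers and reasons for discontinuation are reported by blood group.
- A sensitivity analysis counts patients who discontinue as not improved through one month. It is needed because censoring alone assumes that leavers are not systematically worse than those who stay, which is the very point in doubt. It is deliberately pessimistic and should be read beside the main result.

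The cost is one line deleted in two places, a short paragraph on the analysis set, and an entry on the case record form for the date of last contact and the reason for stopping. The sample size need not change. The change should be made before anyone is removed under the rule, since data not collected after removal may not be recoverable.

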**Research instruments:**

1. Informed consent form.

2. Case record form

**Primary Outcome Measure:**

- 1. Duration required to have clinical improvement

[Time Frame: 1 months]

**Secondary Outcome Measure:**

1. Conversion to the next level of severity

Time Frame: 1 month]

1. Persistent positivity 14 days after initial positivity

[Time Frame: 14 days]

1. Severity of the disease

[Time Frame: 1 month]

1. Development of post COVID syndrome

[Time Frame: 1 month]

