**PART - D**

**Introduction:**

WHO (World Health Organization) first notify about the emergence of COVID-19 infection in Wuhan city, China in Late December^1^. Soon the novel virus became pandemic, declared on 12 March 2020^2^. On 19 September 2020, there have been 30,369,778 confirmed cases of COVID-19, including 948795 deaths reported to WHO^3^. The presentation of COVID-19 varied widely. The most common symptoms of COVID-19 involved fatigue, fever, dry cough, respiratory distress, anosmia and so on. A large proportion of the patient remains Asymptomatic as well^4^. Its behavior also varied among the nations of the universe. Genome wide Association Study on Severe Covid-19 with Respiratory Failure, GWAS Group detected cross-replicating associations with rs11385942 at locus 3p21.31 and with rs657152 at locus 9q34.2. The association signal at locus 9q34.2 coincided with the ABO blood group locus. They found a higher risk among persons with blood group A than with other blood groups^5^.Some other viruses like HBV^6^, SARS-COV^7^, and MERS-COV^8^ have susceptibility relation with ABO blood group. The mechanisms behind the impact of blood group are still unclear. Histo-blood group antigens are also expressed on endothelial cells (EC) and platelets^9^. SARS-CoV enter into human body through the replication in epithelial cells of the respiratory and digestive tracts. They have the ability to synthesize ABH carbohydrate epitopes. It has been hypothesized that the S protein of virions produced by either A or B individuals could be decorated with A or B carbohydrate epitopes, respectively. Guillon et al^10^. Reported that interaction between S protein and ACE-2 is specifically inhibited by human natural anti-A antibodies. SARS-COV and SARS-COV-2 have similar nucleic acid sequence and similar receptor combination with angiotensin-converting enzyme 2 (ACE2)^11^. It was also found that non-A type is a risk factor for venous thromboembolism, which is one of the pathogenesis for COVID-19 death^12^. But different studies showed contradicting results in relation to influence of blood group on susceptibility and outcome of COVID-19 infection^13, 14, 15, 16^. So to observe the impact of ABO blood groups on the presentation and outcome of Confirmed COVID -19 infection, this study was conducted in the largest COVID19 dedicated hospital in Bangladesh.

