**Acute Respiratory Distress Syndrome (ARDS)**

The diagnosis requires clinical and ventilatory criteria. This syndrome is suggestive of a serious new-onset respiratory failure or for worsening of an already identified respiratory picture. Different forms of ARDS are distinguished based on the degree of hypoxia. The reference parameter is the PaO2/FiO2:

- Mild ARDS: 200 mmHg < PaO2/FiO2 ≤ 300 mmHg. In not-ventilated patients or in those managed through non-invasive ventilation (NIV) by using positive end-expiratorypressure (PEEP) or a continuous positive airway pressure (CPAP) ≥ 5 cmH2O.
- Moderate ARDS: 100 mmHg < PaO2/FiO2 ≤ 200 mmHg.
- Severe ARDS: PaO2/FiO2 ≤ 100 mmHg.

When PaO2 is not available, a ratio SpO2/FiO2 ≤ 315 is suggestive of ARDS.

Chest imaging utilized includes chest radiograph, CT scan, or lung ultrasound demonstrating bilateral opacities (lung infiltrates > 50%), not fully explained by effusions, lobar, or lung collapse.

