**Demography**

1. Name: 2. Age: 3. Sex: M / F

4. Address:

5. **Epidemiological link**: Y / N

5. Mobile No:

6. Residency: Urban / Rural

7. Smoker: Y / N

8. Marital Status: Married / Single

9. Education: Literate / Illiterate

Date of starting symptoms

Date of becoming Covid positive

Hospital Admission Date

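### Death is in no outcome, on no severity level and in no case record form field, so a death without a recorded step-up is not a conversion, and any death looks like loss to follow-up

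*Protocol*

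**What the plan says.** The primary outcome is "Duration required to have clinical improvement", over 1 month. The Secondary Outcome Measure section lists "Conversion to the next level of severity" (1 month), "Persistent positivity 14 days after initial positivity", "Severity of the disease" (1 month) and post-COVID syndrome (1 month). Part-G, the abstract for the national ethics committee, repeats the same list. Death appears in neither place.

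The Operational definition section sets out mild illness, moderate pneumonia, severe pneumonia and ARDS. The last level defined is "Severe ARDS: PaO2/FiO2 ≤ 100 mmHg". Patients enter with mild or moderate disease (Inclusion Criteria).

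On follow-up, the Summary states: "They will be followed up for at least 30 days or hospital discharge which one is longer". The Abstract summary for Ethical Committee says the same.

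The Demography part of the Case Record Form asks for the dates of symptom onset and of becoming COVID positive, and then "Hospital Admission Date". The rest of the form holds daily symptoms and vital signs up to D-30, laboratory values up to D-14, imaging findings and a line for post-COVID symptoms.

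The Data analysis section plans a relative risk for group A against non-A and a Kaplan-Meier curve for the duration of recovery.

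**The concern.** This is a study of COVID-19 outcomes in hospital, and it has no planned way to register its worst outcome.

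Two analyses are exposed. In the conversion comparison, a death that no recorded worsening precedes does not satisfy the outcome as worded and falls among the patients who did not convert. In the recovery analysis, a death looks like an interrupted record, and ordinary censoring assumes that the patient could still have recovered afterwards.

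If such deaths are unequally spread over blood groups, the comparison of A with non-A is biased. The protocol gives a reason to consider that: the Introduction links non-A type to venous thromboembolism, "which is one of the pathogenesis for COVID-19 death".

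A statistical analysis plan may choose the method for deaths. It cannot apply that method to a status that was never collected.

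**Working it through.** **Step 1: is death captured anywhere?** The relevant places, side by side:

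| Place | What it holds | Death or end status? |
|---|---|---|
| Primary and secondary outcomes, and their repeat in Part-G | five outcomes | no |
| Severity definitions | mild to severe ARDS | no |
| Follow-up sentence (Summary; Abstract summary for Ethical Committee) | 30 days or discharge, whichever is longer | end by death not addressed |
| Case Record Form, dates | onset, positivity, admission | no discharge or death date |
| Case Record Form, last entry | post-COVID symptoms | no final status |

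Elsewhere death is mentioned only in the background text, in a reference title and in an ethics checklist item about types of records.

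**Step 2: which deaths are affected, and how?** Entry is at mild or moderate, so the next level is moderate or severe pneumonia.
- Death after a recorded step-up: already a conversion, but the later daily columns are blank and the death is not identifiable.
- Death with no recorded step-up: not a conversion as the outcome is worded, and again not identifiable.

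**Step 3: effect on the conversion relative risk.** The protocol states no conversion or death rate, so there is no figure of its own to reproduce and every rate here is an assumption. Let c be the recorded conversion proportion and d the proportion dying with no recorded step-up. Then

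RR recorded = c(A) / c(non-A); RR with deaths = [c(A) + d(A)] / [c(non-A) + d(non-A)].

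With c = 15% and 10%, the recorded RR is 15/10 = 1.50.

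| d in A | d in non-A | RR with deaths |
|---|---|---|
| 0.5% | 0.25% | 15.5/10.25 = 1.51 |
| 0.25% | 0.5% | 15.25/10.5 = 1.45 |
| 2% | 1% | 17/11 = 1.55 |
| 1% | 2% | 16/12 = 1.33 |
| 3% | 2% | 18/12 = 1.50 |

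The last row shows that deaths in the same ratio as conversions leave the RR unchanged.

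The planned 378 patients at 1:2 are 126 in A and 252 in non-A. On that split the assumed conversions are 0.15 × 126 = 18.9 and 0.10 × 252 = 25.2. The fourth row adds 0.01 × 126 = 1.3 and 0.02 × 252 = 5.0 deaths. So about six unregistered deaths move the RR from 1.50 to 1.33.

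**Step 4: effect on the recovery curve.** Take the protocol's planning value of 70% cured by day 12 in group A and assume that a proportion m dies. If all deaths fall before the first recovery and are censored, the Kaplan-Meier estimate at day 12 is 0.70/(1 − m):
- m = 1%: 0.70/0.99 = 0.707
- m = 5%: 0.70/0.95 = 0.737

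The proportion actually recovered is 0.70 in both cases. Later deaths shift the estimate less.

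**Step 5: number of deaths.** For the 416 patients planned, assumed overall mortality of 1%, 3% or 5% means about 4, 12 or 21 deaths. The dropout allowance is 416 − 378 = 38 patients, so deaths could sit unnoticed inside the expected loss.

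**The case against.** The strongest reply is that the protocol is silent on death and does not mishandle it. No sentence says that a death counts as not converted, and the handling of deaths in an analysis is commonly left to the statistical analysis plan. This stands for the choice of method. It does not stand for data collection or for the outcome definition, both of which this document fixes.

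A second reply is that the form may be incomplete. As shown it has no field for ABO group either, which is the exposure, and the ethics abstract mentions an enclosed data form and the use of indoor hospital records. This is a fair caution. But the form runs from patient ID to the investigator's sign-off, and the records are to be used for filling in the data sheet, which has no place for a death.

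A third reply is that few deaths without prior worsening should occur in a cohort that enters mild or moderate, with respiratory rate and oxygen saturation charted daily. That limits the size, as the 0.5% and 0.25% rows show.

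A reader might also infer more than the documents support:
- *Every death without recorded ARDS counts as not converted.* A step to moderate or severe pneumonia already counts.
- *A death cannot be told from going home.* Daily columns continue to D-30 and follow-up lasts at least 30 days, so a discharged patient should still have entries. The confusion is with loss to follow-up.
- *The bias has a known direction.* The Introduction points to non-A, while the title of the reference it cites there says non-O. Neither describes deaths without respiratory worsening.

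**Conclusion.** The point holds. Death is in no outcome, on no severity level and in no field of the form as shown, although the length of follow-up depends on a discharge date that the form does not ask for. Deaths without a recorded step-up drop out of the conversion outcome, and all deaths resemble loss to follow-up in the recovery analysis.

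The size is unknown. In the illustration the RR with deaths lies between 1.45 and 1.51 at the low assumed rates and between 1.33 and 1.55 at the higher ones, against 1.50 recorded. A wider spread needs larger assumed rates: 6% and 3% give 21/13 = 1.62, and the reverse gives 18/16 = 1.13. Nothing in the documents supports such rates. The figures with deaths are also relative risks for a composite endpoint, so they should not be read as the true value of the conversion RR.

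The conclusion rests on the form being complete as shown. It does not depend on the sample size calculation.

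**What to change.** 1. Add one end-of-follow-up block to the Case Record Form: date, and status as discharged improved, still in hospital, died or lost.
2. In the Secondary Outcome Measure section and its repeat in Part-G, state that death from any cause within 1 month counts as conversion, and show the components separately.
3. In the recovery analysis, treat a patient who dies as never recovered within the 1-month frame, or treat death as a competing event. Do not censor deaths in the ordinary way.
4. Report 30-day deaths by blood group.

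The cost is one block on the form, filled from the indoor records already in use, and a few lines of text. The one downside is that conversion becomes a composite, which is why its components should be reported. Separate reporting of deaths alone would be the minimum, but it would leave the conversion outcome undefined for patients who die without stepping up.

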**Data analysis**:

To compare the groups one way ANOVA was done for continuous variable, Chi square for categorical variables. For outcome assessment relative risk (RR) with 95% CI was measured for qualitative variable categorizing blood group-A and non-A (Group-B, AB, O). Survival analysis by Kaplan-Meier curve was done for the duration of recovery.

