**Investigations Profile**

| **Trait** | **Value** |  |  |  |  |  |
| --- | --- | --- | --- | --- | --- | --- |
|  | **Admission** | **D-3** | **D-5** | **D-7** | **D-10** | **D-14** |
| **Hb** |  |  |  |  |  |  |
| **WBC** |  |  |  |  |  |  |
| **Neutrophil** |  |  |  |  |  |  |
| **Lymphocyte** |  |  |  |  |  |  |
| **Platelet** |  |  |  |  |  |  |
| **ESR** |  |  |  |  |  |  |
| **CRP** |  |  |  |  |  |  |
| **RBS** |  |  |  |  |  |  |
| **Creatinine** |  |  |  |  |  |  |
| **SGPT** |  |  |  |  |  |  |
| **D-Dimer** |  |  |  |  |  |  |
| **Na** |  |  |  |  |  |  |
| **K** |  |  |  |  |  |  |
| **ECG** |  |  |  |  |  |  |
| **Covid-19**  **RT-PCR** |  |  |  |  |  |  |

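### Persistent PCR positivity is defined from the first positive test, but the case record form times its swabs from admission; the form also has no field for ABO group or discharge date

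*Protocol*

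**What the plan says.** **Outcome.** The Secondary Outcome Measure list includes "Persistent positivity 14 days after initial positivity", with a 14-day time frame. The Summary uses the same starting point: "Persistence of RT-PCR positivity 14 days after initial positivity will be determined". The abstract for the national ethics committee repeats the outcome unchanged.

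**Swab schedule.** The case record form's table headed "Investigations Profile" has an RT-PCR row with columns Admission, D-3, D-5, D-7, D-10 and D-14. D-14 is the last column, and no space is labelled for the date of each swab. The symptom and observation grids begin at admission and continue with D2, D3 and so on.

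**Dates.** The Demography page has separate entries for "Date of becoming Covid positive" and "Hospital Admission Date".

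**Exposure.** The Summary says "Their blood group will be determined", and the Data analysis section compares group A with the other three groups combined. Research instruments lists two items, the consent form and the "Case record form". As printed, that form has no entry for blood group.

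**Follow-up.** The Summary and the abstract for the ethical committee follow each patient to 30 days or to discharge, whichever comes later. The form has no discharge date.

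**The concern.** The outcome and the form use different day zeros. The form itself treats first positivity and admission as different dates, eligibility does not require them to coincide, and no section equates them. If the D-14 column is taken as the day-14 result, patients are tested at differing intervals after first positivity. Where positivity falls with time, a late swab understates persistence at day 14. If the delay to admission also differed between blood groups, the comparison itself would be biased.

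The second matter is simpler. Every comparison in the study is by ABO group, yet the data form provides no place to write it.

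**Working it through.** **1. Fields on the form.** Going through its pages as printed:

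- Demography: identity, social items, and dates of symptom onset, first positivity and admission.
- Clinical features: daily symptoms to D-30.
- Observations: daily temperature, pulse, blood pressure, respiratory rate and oxygen saturation to D-30, with co-morbidity once.
- Investigations: 15 rows, from Hb to RT-PCR.
- Imaging, and a line for post-COVID symptoms.

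ABO group and discharge date appear on none of them.

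**2. Which day zero the form uses.** The symptom grid runs from admission straight to D2, so admission is D1. The investigation table also opens at admission. The repeat PCR appears only there.

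**3. Timing of each swab.** Let lag = admission date minus date of first positivity. With admission as D1, the swab at form day d falls on

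day since first positivity = lag + d − 1.

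The D-14 swab thus falls on lag + 13. Setting lag + 13 = 14 gives lag = 1. If admission is counted as day 0, it falls on lag + 14, and the match is at lag = 0. The documents state no lag, so the table covers an assumed range of 0 to 12 days (admission = D1).

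| Lag (days) | D-14 swab falls on day | Scheduled swab nearest day 14 | Distance (days) |
|---|---|---|---|
| 0 | 13 | D-14 (day 13) | 1 |
| 1 | 14 | D-14 (day 14) | 0 |
| 2 | 15 | D-14 (day 15) | 1 |
| 3 | 16 | D-10 (day 12) or D-14 (day 16) | 2 |
| 4 | 17 | D-10 (day 13) | 1 |
| 5 | 18 | D-10 (day 14) | 0 |
| 6 | 19 | D-10 (day 15) | 1 |
| 7 | 20 | D-7 (day 13) | 1 |
| 8 | 21 | D-7 (day 14) | 0 |
| 9 | 22 | D-5 (day 13) or D-7 (day 15) | 1 |
| 10 | 23 | D-5 (day 14) | 0 |
| 11 | 24 | D-3 (day 13) or D-5 (day 15) | 1 |
| 12 | 25 | D-3 (day 14) | 0 |

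**4. Reading the table.** Used alone, the D-14 swab is 2 days late at lag 3, 4 days late at lag 5 and 6 days late at lag 7. Taking the nearest scheduled swab instead, the distance is never more than 2 days, and exceeds 1 day only at lag 3.

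**5. Effect on the comparison of blood groups.** If the lag has the same distribution in group A and non-A, and positivity declines in the same way in both, late swabs lower both rates without creating a difference. A spurious difference needs a lag that varies with blood group. The documents neither report nor suggest one, so no figure for such a bias can be derived from them.

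**The case against.** The strongest reply is that the planned data nearly suffice. Both anchor dates are recorded, six swabs are scheduled, and one of them is always close to day 14 over the assumed lags. Visit windows commonly belong in a statistical analysis plan, which is not shown. This stands as a limit on the size of the problem. It does not remove the contradiction: the protocol fixes one day zero in the outcome and another in the form, and without swab dates or a selection rule the D-14 column is the obvious one to use.

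A reader might infer more than the documents support, in four ways:

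- *That the study does not collect its exposure.* The Summary plans to determine blood group, and the abstract for the ethical committee allows hospital records to be used to complete the patient data sheet. The defect is that the form has no place for the result.
- *That persistent positivity will differ falsely between blood groups.* This needs a difference in lag by blood group, which is not documented.
- *That severity cannot be graded.* Mild, moderate and severe illness are defined largely by symptoms, respiratory rate and oxygen saturation, which the form records daily. Only the ARDS grades lack their inputs, since the form has no PaO2 or FiO2 entry.
- *That a date of death is missing for a listed outcome.* Death is not among the primary or secondary outcomes.

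**Conclusion.** The point holds in a limited form. Followed as written, the D-14 swab measures the defined outcome only for patients admitted within about 0 to 1 days of their first positive test. For others it is late by the lag (admission as day 0) or by the lag minus 1 (admission as D1). The share of patients affected is unknown, because the documents give no lag. Choosing the nearest scheduled swab brings the error within 2 days for lags of 0 to 12 days, assuming the swabs are taken as scheduled. Bias between blood groups is possible only if the lag differs between them.

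The missing ABO field is a plain form omission, but it concerns the variable on which every comparison depends. The missing discharge date leaves the follow-up rule without a recorded endpoint for patients who stay in hospital past D-30, where the daily grids stop.

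The reach is one secondary outcome plus a form omission. The definition of the primary outcome, time to clinical improvement, is not affected.

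**What to change.** 1. Use one anchor for persistent positivity, in either of two ways:
   - date the day-14 swab from the recorded date of first positivity; or
   - keep the present schedule, record the date of every swab, and define the outcome from the scheduled swab nearest day 14 after first positivity. State the window (2 days covers lags of 0 to 12 with admission as D1), a rule for ties such as those at lags 3, 9 and 11, and how patients with no swab in the window are handled.
2. State on the form whether admission is day 0 or day 1.
3. Add an ABO group field and a discharge date to the case record form.

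The cost is a short form revision and one outcome sentence. No test is added: the first option moves a planned swab and the second changes only how planned swabs are used. If enrolment has already begun, the second option remains available wherever swab dates can be recovered from hospital records.
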